### Control group

The control group will receive written information about the benefits of being active (i.e. the Choose Health: Be Active booklet) and will be provided with their accelerometer data readings during the one face-to-face meeting they have. Like the intervention group, they will be provided with information about what participant should do in the event of a fall. They will also be encouraged to join a falls prevention class if they have not participated in one in the preceding 12 months. No goals will be set and they will not receive any fortnightly phone calls to minimize any confounding motivational effects that might occur. Therefore, the only addition over and above usual care would be the provision of their baseline status from the first accelerometer assessment.

### Primary outcomes

#### Feasibility

Feasibility indicators include the trial process (recruitment, retention, acceptability, adherence and safety) in the study. Adherence to the intervention will be assessed according to completion of the goals set and fidelity to phone calls and visits. Acceptability of the intervention will be assessed with a questionnaire.

#### Sedentary time

Total sedentary time will be measured by ActivPAL™ (PAL Technologies Ltd., Glasgow, UK), a small (35 × 53 × 7 mm, 15 g) uniaxial accelerometer-based device attached anteriorly on the right mid-thigh held in place by a waterproof dressing (3 M Tegaderm transparent dressing) for 24 h over 7 days. This device uses accelerometer-derived information about thigh position to estimate time spent in different body positions (i.e sitting or lying, standing and stepping). Data will be collected for a 1-week period and processed in 15-s epochs using the ActivPAL™ software (version 5.8.3). The ActivPAL™ has been tested for reliability and validity, has been used with older adults and is considered the current most valid objective measure of sedentary behaviour [20]. The duration spent sitting, standing, lying and moving daily will be quantified.

### Secondary outcomes

Secondary outcomes measured include self-reported sedentary time, FES, change in gait speed and proportion of fallers and numbers of falls. Self-reported sedentary time will be evaluated using the validated MOST questionnaire [30]. Fear of falling will be assessed using the self-reported short-form FES International [31]. Gait speed will be assessed during a 6-m walk. The number of falls in each participant will be assessed during the 6 months of the study by self-report. Explanation will be provided to participants that a fall is defined as an event during which a person inadvertently comes to rest on the ground, floor or other lower level [42].

### Assessments

Assessment of outcome measures will occur at three time points—baseline (T0), week 12 (T12) and week 24 (T24). Assessments performed at these time points are summarized in Table 4.

**Table 4 Tab4:** Methods and timing of assessing variables in this study

Variables	Measure	When	Time to complete
BMI (weight and height)	Calibrated digital scales and stadiometer	T0, T12, T24	1 min
Cognition	Rapid Cognitive Screen	T0	5 min
Cognition	Trail Making Test	T0, T12, T24	8 min
Mood	Geriatric Depression Screen-Five Item	T0	2 min
Frailty	FRAIL screen	T0	2 min
Personality	10-item personality inventory	T0	3 min
Self-reported physical activity	IPAQ—Elderly	T0, T12, T24	5 min
Self-reported sedentary behaviour	MOST questionnaire	T0, T12, T24	5 min
Social Engagement	Lubben Social Network	T0	2 min
Review of falls episode	History-taking	T0, T6, T12, T24	5 min
Fear of falling	Falls efficacy scale	T0, T12, T24	4 min
Activities of daily living	Katz ADL	T0, T12, T24	5 min
Quality of life	EQ5D	T0, T12, T24	2 min
Nutritional status	Mini-nutritional assessment—short-form	T0, T12, T24	2 min
Gait speed	SPPB	T0, T12, T24	2 min
Grip strength	SPPB	T0, T12, T24	5 min
Balance test	Berg Balance	T0, T12, T24	15–20 min
Appendicular lean muscle mass	Bioelectrical impedance	T0, T12, T24	5 min
Motivation to change	Change Questionnaire	T0, T6, T12, T24	5 min
Goal attainment	Goal Attainment Scale	T0, T6, T12, T24	3–6 min
Sedentary time	Accelerometer	T0, T12, T24	
Step counts	Pedometer	T6, T12, T24	2 min
Pedometer adherence	Pedometer	T6, T12, T24	5 min
Neighbourhood Environment	NEWS	T0	15 min

*ADL* activities of daily living, *BMI* body mass index, *IPAQ* International Physical Activity Questionnaire, *MOST* Measure of Older Adults’ Sedentary Time, *NEWS* Neighbourhood Environment Walkability Scale, *SPPB* Short Performance Physical Battery

Demographic information will be collected at T0. This information includes date of birth (age), ethnicity, living arrangement, comorbid conditions and medication use. The Charlson comorbidity index (CCI) will be applied to measure the burden of disease and thus enable confounder adjustment of the results [43]. The index is based on 22 clinical conditions. Each condition is given an associated weight (1, 2, 3 and 6) according to the gravity of the disease.

Anthropometrics include height (m), weight (kg) and body mass index (BMI) (kg/m^2^). To ensure accurate measurement, height will be measured to the nearest 0.01 unit and weight to the nearest 0.1 unit. Participants will be instructed to remove their shoes and any bulky clothing before measurement. Height will be measured using a portable stadiometer, and weight will be measured using a calibrated electronic scale.

A ten-item personality inventory will be completed by the participants at baseline to determine their Big-Five personality domains [44]. Self-report of the ability to perform personal activities of daily living (ADLs) were assessed using the Katz ADLs [45]. The Luben Social Network Scale will be used to assess the level of social engagement [46]. Generic physical activity and sedentary behaviour will be self-reported using the elderly version of the International Physical Activity Questionnaire (IPAQ) [47] and a validated sedentary behaviour questionnaire measuring older adults’ sedentary time (MOST) [30]. Participants will also complete the Neighbourhood Environment Walkability Scale (NEWS). This scale will assess participants’ perception of neighbourhood design features related to physical activity, including residential density, land use mix (including both indices of proximity and accessibility), street connectivity, infrastructure for walking/cycling, neighbourhood aesthetics, traffic and crime safety and neighbourhood satisfaction [48]. The European Quality of Life (EQ5D) scale will be used to estimate the health status and quality of life [49]. Mood will be assessed using the Geriatric Depression Scale—five-items [50].

Physical function will be assessed objectively using the short physical performance battery [51]. Total functional capacity is based on a composite score from the following subtests: repeated chair stands, balance (semi-tandem, side-by-side stand, tandem stand) and 6 m walk to assess gait speed. Bergs Balance Scale will be used to measure balance [52]. Grip strength will be measured using the Jamar hand dynamometer (Model J00105 JAMAR Hydraulic Hand Dynamometer, Sammons Preston, Bolingbrook, IL, USA) with the dominant hand in a seated position with their feet firmly on the ground and back straight against the chair (to prevent participant movement) [53]. Three trials will be made with a pause of about 10 to 20 s between each trial to avoid the effects of muscle fatigue. Maximum grip strength is then recorded.

The Trail Making Test is a neuropsychological test of visual attention and task switching. It consists of two parts in which the subject is instructed to connect a set of 25 dots as quickly as possible while still maintaining accuracy. The test can provide information about visual search speed, scanning, speed of processing, mental flexibility, as well as executive functioning [54]. It is sensitive to detecting cognitive impairment associated with dementia [55]. Fear of falling will be assessed using the self-reported short-form FES International [31].

Appendicular skeletal muscle mass (ASM) will be assessed using the single frequency Quantum II Body Composition Analyzer (RJL Systems, Clinton Township, MI, USA). This device produces a 425 μA constant sinusoidal current at a single frequency of 50 kHz ± 1%. Participants will be asked to remove their shoes, socks and jewelry. Bioelectrical impedance analysis (BIA) measurements are performed with participants in a supine position, with their arms positioned by their sides and palms facing down on a non-conductive examination chair. Two electrodes are placed on the right wrist and two others on the right ankle. On the wrist, one electrode is placed on the dorsal aspect next to the ulnar head and another is placed on the dorsal surface of the first joint of the middle finger. On the ankle, one electrode is placed on an imaginary line bisecting the medial malleolus and the other electrode on the base of the second toe. The device reports resistance and reactance values. ASM will be estimated using the prediction equation by Sergi et al [ASM (kg) = − 3.964 + (0.227 × RI) + (0.095 × weight) + (1.384 × sex (men = 1, women = 0) + (0.064 × Xc) where RI: resistance index, Xc: reactance] [56].

### Focus groups

We will conduct four focus groups with participants from the intervention (two groups) and control (two groups) arms at the end of the intervention at week 24. These sessions will consist of groups with four to eight individuals and last for 1.0 to 1.5 h. A trained professional will facilitate these focus groups, with the assistance of a second researcher. The focus groups will evaluate feasibility, including acceptability, and evaluate how the accelerometer and pedometer affected the participants and their behaviours. For the intervention group, the perceived effectiveness of the SMART-MOVE health coaching will also be explored. With consent, focus groups will be audio recorded and transcribed. Thematic analysis will be conducted, focusing on analysing the data to answer the research questions as well as using an inductive approach.

### Statistical analyses

Feasibility findings will be primarily descriptive and used as a metric for improvement when compared to similar studies. We hypothesize that the intervention will be feasible among several improvement metrics including 40% or more recruitment rate and less than 20% attrition. This hypothesis is based on findings from earlier studies [13–16].

Descriptive analyses will be conducted using mean with standard deviation, median with interquartile range and frequency for baseline characteristics. These characteristics include age, gender, ethnicity, physical function, health status, quality of life and mental status. Mean group differences will be examined using independent samples *t* test for normally distributed data and nonparametric tests (Kruskal-Wallis and Mann-Whitney *U*) for non-normally distributed data. Differences in frequency of variables will be compared using chi-square test.

Analysis of variance (ANOVA) will be used to test the post-intervention difference at 12 and 24 weeks between the two groups. The covariates in the analysis will include baseline values of the dependent variable and any variable significantly different between groups at baseline. Group mean values for adherence variable at 12 and 24 weeks (retention rate, days the accelerometer and pedometer are worn) will be analysed by an independent *t* test. The data analysed will be based on the intention-to-treat analysis.

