## Aims

The primary aim of this trial is to evaluate the feasibility and effect of a goal-setting health coaching intervention based on initial accelerometer and then pedometer feedback on total sedentary time for 12 weeks compared to one-off advice through a brochure in reducing sedentary behaviour in older people at high risk of falling according to the STEADI criteria (had a fall in last 12 months, feel unsteady when walking or standing, and/or worry about falling) [29].

The secondary aims are to compare the change in sedentary time based on the self-reported Measure of Older Adults' Sedentary Time (MOST) questionnaire [30], FES [31], change in gait speed, proportion of fallers and numbers of falls.

Evaluation of effects at 24 weeks will also occur to determine if the changes seen with the intervention compared to control is sustained at 24 weeks.

It is hypothesized that the intervention will be feasible with a 40% recruitment rate and an 80% retention rate will be achieved at 6 months. For adherence and acceptability, it is hypothesized that goal attainment scale of 0 (indicating goal achieved) for at least three goals will be achieved in 70% of participants (intervention group) and the intervention is acceptable in 70% of the participants. A further hypothesis is that the intervention is effective in reducing sedentary time and the benefits sustained at 24 weeks.

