6. How	The intervention will be tailored to suit the participant daily activities. SMART (specific, measurable, attainable, relevant, time-bound) goals will be set. At the first face-to-face meeting, participants will set three goals to reduce sedentary behaviour. One goal will be incrementally introduced every 2 weeks so that by week 6, the participant will be working on three goals. At the second face-to-face meeting, the participant will set another three goals that will be added incrementally every fortnight. Participants in the intervention arm will be provided with information about their duration of time spent upright (accelerometer) and total number of steps (pedometer) taken each day. Goals are set to increase their time spent upright and total number of steps taken. Participants will calculate the mean daily steps over 7 days and increase by 200 steps from the mean per week as a goal. They will also be encouraged to attend falls prevention classes if they have not participated in one in the preceding 12 months.
7. Where	The intervention will be delivered to community-dwelling older people who had at least one fall in the last 12 months or are at risk of one. It will be delivered at Adelaide G-TRAC Centre or The Queen Elizabeth Hospital.
8. When and how much	The face-to-face assessment, goal setting and health-coaching will occur at the beginning of the intervention period and will last approximately 2 h. An accelerometer will be worn for one week before this face-to-face coaching. Phone coaching will occur for up to 15 min fortnightly when there is no face-to-face coaching. At week 6, a second face-to-face coaching will be conducted where goals will be reviewed and additional goals set.
9. Tailoring	The recommended physical activity plan will be tailored to individual needs based on participants’ goals, baseline levels, preferences and physical ability.

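### The only named test that fits the proportion of fallers cannot use the fall history taken at T0; a pre-specified adjusted comparison would be a free, minor improvement

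*Protocol article*

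**What the plan says.** The Secondary outcomes section lists "change in gait speed and proportion of fallers and numbers of falls". In Statistical analyses, the paragraph that opens with "Descriptive analyses will be conducted using mean with standard deviation, median with interquartile range and frequency for baseline characteristics" closes with "Differences in frequency of variables will be compared using chi-square test". The Abstract repeats the chi-square sentence after its list of outcomes, without the baseline setting. Neither place names the fallers outcome.

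The next paragraph of Statistical analyses turns to follow-up: "Analysis of variance (ANOVA) will be used to test the post-intervention difference at 12 and 24 weeks between the two groups". Adjustment is attached there: "The covariates in the analysis will include baseline values of the dependent variable and any variable significantly different between groups at baseline".

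On the cohort, Aims gives the risk criteria as "had a fall in last 12 months, feel unsteady when walking or standing, and/or worry about falling", and Table 1 describes "community-dwelling older people who had at least one fall in the last 12 months or are at risk of one". People with and without a recent fall can therefore both enter. Table 4 schedules "Review of falls episode" by history-taking at T0, T6, T12 and T24. Randomisation and blinding stratifies by sex only. The Discussion concedes that the study is too small to assess falls rates.

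**The concern.** A fall in the past year is one of the plan's own markers of high risk, and it is known for every participant before allocation. The plan accepts in principle that the baseline value of an outcome should enter its analysis, but neither named method delivers this for a yes/no falls outcome. The chi-square takes no covariate, and the ANOVA is a normal-theory model.

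With 32 to 40 people per arm and no stratification on fall history, the share of prior fallers can differ noticeably between arms by chance. In such a trial the crude difference in fallers partly reflects who was allocated where. The safeguard of adding variables that differ significantly at baseline may not respond, because a test at this sample size misses imbalances large enough to move the result. At stake is how the falls estimate of a pilot study is read; the sedentary-time outcome is not affected.

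**Working it through.** **Inputs from the protocol.** Power calculation: 64 evaluable participants, 20% attrition, 80 recruited (40 per arm). This reproduces: 64 / (1 − 0.20) = 80, so n per arm runs from 32 (evaluable) to 40. No rate, power or sample size is given for falls.

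**Assumptions, not in the protocol.** Share of prior fallers p: 30–70%. Six-month fall risk in prior fallers versus others: 40% vs 20%, 50% vs 25%, or 60% vs 20%.

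**1. How often imbalance occurs.** For p = 0.5, the SD of the between-arm difference is about √(2p(1−p)/n):
- n = 40: √(0.5/40) = 0.112. P(≥ 20 points) = P(|Z| ≥ 1.79) = 0.07.
- n = 32: √(0.5/32) = 0.125. P(≥ 20 points) = P(|Z| ≥ 1.60) = 0.11.

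The exact hypergeometric distribution over p = 30–70% gives 27–50% for at least 10 points and 8–12% for at least 20 points. It differs from the normal figures because the attainable imbalances are discrete. Taken together, 20 points or more occurs in roughly 7–12% of trials.

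**2. What it does to the falls comparison.** Shift = imbalance × (risk in prior fallers − risk in others).
- 10 points: 0.10 × 0.20 = 2 points, up to 0.10 × 0.40 = 4 points.
- 20 points: 0.20 × 0.20 = 4 points, up to 0.20 × 0.40 = 8 points.

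The sampling SE of the difference is √(2q(1−q)/n), with q the overall fall risk. It runs from about 10 points (q = 0.26, n = 40: √(2 × 0.26 × 0.74/40) = 0.098) to 12.5 points (q = 0.48, n = 32: √(2 × 0.48 × 0.52/32) = 0.125).

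**3. Whether the baseline-significance rule would catch it.** At exactly 20 points and p = 0.5:
- n = 40: z = 0.20/0.112 = 1.79, p-value about 0.07.
- n = 32: z = 0.20/0.125 = 1.60, p-value about 0.11.

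At p = 0.3 or 0.7 and n = 40, SE = √(2 × 0.21/40) = 0.102 and z = 1.95, still just short of 1.96. Larger imbalances can trigger the rule: 25 points at n = 32 and p = 0.5 gives z = 0.25/0.125 = 2.00. The rule therefore often misses a 20-point imbalance, but not every imbalance above it.

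**4. Error rates and power.** Simulation of 200,000 runs, unadjusted chi-square against a Mantel-Haenszel test stratified by prior fall:

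| Quantity | Chi-square | Stratified |
|---|---|---|
| Type I error, all trials | 4.7–6.0% | 4.8–5.0% |
| Type I error, given about 20 points of imbalance | 5.8–10.5% | 4.9–5.2% |
| Power at within-stratum odds ratio 0.3 | 40–64% | 40–67% |

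Within scenarios, power changes by about −1 to +6 points.

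**5. Power for fallers in any case.** With a 40% control risk (assumed) and relative risk 0.7, power is 17% (n = 32) to 20% (n = 40). At relative risk 0.5 it is 41–50%.

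**The case against.** A reader might infer that the plan commits to an unadjusted chi-square for fallers. It does not say so. In Statistical analyses the sentence closes a paragraph about baseline characteristics, and in the Abstract it names no outcome. The covariate rule in the next paragraph could be meant for all outcomes, and for fallers the natural baseline value is fall history. The section on Assessments also collects a comorbidity index to allow confounder adjustment. The covariates for a secondary binary outcome are commonly left to an analysis plan. All of this stands as a limit on the claim. What remains is that whichever reading is taken, no named method both fits a proportion and uses the T0 fall history.

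A second tempting reading is that imbalance biases the falls result. It does not. Over randomisations the shift averages zero, the unadjusted SE already allows for it, and overall type I error stays near 5%. The usual shift is well below the sampling error.

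Third, the risk gap is assumed. The Participants section requires everyone to reach a STEADI score of 4 and a FRAIL score of 1, so enrolled non-fallers are high-risk too. A gap of 10 points instead of 20–40 would cut the shift at 20 points of imbalance to 0.20 × 0.10 = 2 points. This objection stands as a caution on size.

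**Conclusion.** The point holds as a minor refinement. The chi-square is the only named test that fits the proportion of fallers, it cannot use a prognostic variable already collected in both arms, and the adjustment rule is tied to a model unsuited to a yes/no outcome.

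The size is modest. In roughly 7–12% of trials the arms would differ by 20 points or more in prior fallers. At about 20 points the crude difference moves by 4–8 points and the conditional type I error of the chi-square rises to 5.8–10.5%. Averaged over all trials there is no bias and little gain in power. These figures rest on assumed fall risks and an assumed share of prior fallers.

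A reader might also translate the gain into a sample-size saving. With half prior fallers and risks of 45% and 20%, the variance explained is 0.25 × 0.25² / (0.325 × 0.675) = 0.071. That is a linear-model figure. It does not carry over to a logistic odds ratio, where adjustment changes the quantity being estimated. Nor would adjustment rescue an outcome that the protocol already calls underpowered.

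**What to change.** Add one sentence to Statistical analyses: the proportion of fallers will be compared as a risk difference or risk ratio with 95% CI, adjusted for a pre-specified T0 covariate, fall in the past 12 months (yes/no). Suitable methods are Mantel-Haenszel estimation stratified by prior fall, or Poisson regression with robust standard errors. Include the same covariate in the model for the number of falls. Fix it in advance, so that its use does not depend on a baseline significance test.

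The cost is the sentence itself. Falls history is already scheduled at T0 for both arms; the T0 form need only capture the 12-month yes/no item. At an assumed overall risk of 32.5%, 64 to 80 participants give about 21 to 26 fallers (0.325 × 64 = 20.8; 0.325 × 80 = 26), enough for treatment plus one binary covariate.

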**Methods:**

A single-blinded randomized controlled feasibility trial involving 80 community-dwelling people aged 65 years and above will be conducted with 40 randomized to the intervention and another 40 to control. Primary outcomes will be the feasibility of the intervention and change in total sedentary time at 12 and 24 weeks. Secondary outcomes include a change in fear of falling based on the falls efficacy scale, gait speed, self-reported sedentary time, the proportion of fallers and number of falls. Four focus groups (two from each arm) will be conducted at the end of the study to evaluate the feasibility and effectiveness of this intervention. Feasibility findings will be primarily descriptive. Mean group differences will be examined using independent samples *t* test for normally distributed data and nonparametric tests (Kruskal-Wallis and Mann-Whitney *U*) for non-normally distributed data. Differences in frequency of variables will be compared using chi-square test. Analysis of variance (ANOVA) will be used to test the post-intervention difference between the two groups at 12 and 24 weeks.

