### Randomisation and blinding

Randomisation and allocation of a participating group to intervention will take place after each participant have provided their consent and completed the baseline assessment. To ensure allocation concealment, the allocation will be determined after baseline data collection using a sealed envelope technique. The randomisation sequence will be computer-generated (https://www.randomizer.org/). We will stratify randomisation by sex, to allow equal numbers of men and women in each group. The research assistants in charge of collecting and entering all outcome data will be blinded to intervention allocation throughout the trial. Participants will be informed not to reveal their group allocation to the research assistants performing the assessments. Additionally, research assistants will be informed not to ask participants which group they are allocated to. Research assistants will be trained to ensure consistency with data collection. The number of participants in whom the research assistants are inadvertently unblinded at follow-up will be recorded.

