### Power calculation

Sixty-four participants will be required to detect a 30 min/day reduction [15] in sedentary time (80% power, alpha 0.05) in the interventional group, assuming there is no change in the control arm. Therefore, the aim is to recruit 80 participants (40 in each arm) to allow for 20% attrition. The same number of male and female participants will be recruited.

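### The sedentary-time model takes its covariates from baseline significance tests and does not name sex, the stratification factor; this leaves the model open and usually costs power, but does not inflate type I error

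*Protocol article*

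**What the plan says.** Change in total sedentary time is one of the two primary outcomes (Abstract, Methods): "Primary outcomes will be the feasibility of the intervention and change in total sedentary time at 12 and 24 weeks". The test is given under Statistical analyses: "Analysis of variance (ANOVA) will be used to test the post-intervention difference at 12 and 24 weeks between the two groups". The next sentence fixes the covariates: "The covariates in the analysis will include baseline values of the dependent variable and any variable significantly different between groups at baseline". An ANOVA with these covariates is in effect an ANCOVA.

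The same section lists what will be described at baseline: "These characteristics include age, gender, ethnicity, physical function, health status, quality of life and mental status". It names tests for group differences but gives no significance level for admitting a covariate and no closed list of candidates.

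Randomisation and blinding says: "We will stratify randomisation by sex, to allow equal numbers of men and women in each group". Sex is not named as a covariate. Assessments says of the comorbidity index: "The Charlson comorbidity index (CCI) will be applied to measure the burden of disease and thus enable confounder adjustment of the results". The index is not named in the model either.

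The Consent section adds that data are analysed only once the study is complete, so the baseline tests that choose the model would be run when outcomes already exist.

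**The concern.** After proper randomisation, any significant baseline difference is due to chance. Its p-value measures how unbalanced a variable happens to be and says nothing about whether that variable predicts sedentary time. A strong predictor that is balanced stays out, and an irrelevant variable that is unbalanced comes in.

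Three things follow. The adjusted estimate of a primary outcome comes from a model that nobody can write down in advance. The standard error and p-value of that model take no account of the selection step. And the stratifier is treated backwards: stratification makes a significant sex difference very unlikely, so the rule almost guarantees that the one variable that constrained the allocation is left out. Standard practice is to adjust for it.

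At stake are the pre-specification of the sedentary-time analysis and some precision in a trial that expects about 64 evaluable participants.

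**Working it through.** **The plan's own figure.** Power calculation says: "Sixty-four participants will be required to detect a 30 min/day reduction", with 80% power and alpha 0.05. No SD is given, so 64 can only be solved backwards. With 32 per arm and two-sided alpha (assumed), SD = 30 / [(1.96 + 0.84) × √(2/32)] = 42.8 min/day by the normal formula; the exact t test gives 42.2, a standardised difference of 0.7115. The attrition step reproduces: 64 / (1 − 0.20) = 80.

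**How many candidates.** Table 4 lists 22 measures at T0. Goal attainment is set only in the intervention arm, and accelerometer sedentary time is already in the model as the baseline outcome, which leaves 20. Assessments adds age, ethnicity, living arrangement, comorbid conditions, medication use and the Charlson index (26), and sex makes 27. At the other end, Statistical analyses names seven characteristics, though only as examples.

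**Chance that the model changes.** With k independent candidates, each tested at 5% (assumed), P(at least one enters) = 1 − 0.95^k:

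| k | P(at least one) |
|---|---|
| 7 | 30% |
| 10 | 40% |
| 20 | 64% |
| 27 | 75% |

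With 27, the expected number is 27 × 0.05 = 1.35. Sex can hardly differ under stratification; without it, 1 − 0.95^26 = 74%. Correlated candidates lower these figures.

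**Size and power, set A.** Simulation assumptions: 32 per arm, 1:1 within sex, baseline–outcome correlation 0.6, true effect 0.7115 residual SD, 6,000 runs per setting. The rule (baseline value plus whatever is significant, no sex) is compared with a fixed model (baseline value plus sex). The first column gives the share of residual variance explained. Each cell shows 10 / 20 candidates.

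| Setting | Size, rule | Size, fixed | Power, rule | Power, fixed |
|---|---|---|---|---|
| Nothing prognostic | 0.052 / 0.051 | 0.053 / 0.049 | 0.779 / 0.758 | 0.800 / 0.794 |
| Candidates 30%, sex 5% | 0.038 / 0.040 | 0.052 / 0.048 | 0.792 / 0.777 | 0.810 / 0.813 |
| Candidates 50%, sex 10% | 0.026 / 0.029 | 0.047 / 0.049 | 0.807 / 0.786 | 0.832 / 0.831 |
| Sex 20% only | 0.029 / 0.031 | 0.052 / 0.051 | 0.795 / 0.771 | 0.876 / 0.868 |

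The power gaps run from about 2 points (0.810 − 0.792) to about 10 (0.868 − 0.771). The mean estimate was 0.71 under every model, so there is no bias. The Monte Carlo standard error of a 5% size is √(0.05 × 0.95 / 6,000) = 0.003.

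**Size and power, set B.** Here n = 64, with coefficient 0.6 for the baseline value, 0.3 for each of three candidates, residual SD 0.8, effect 0.7 and 5,000 runs:

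| Candidates | Sex effect | Power, rule | Power, fixed | Gap (points) |
|---|---|---|---|---|
| 27, independent | 0.8 | 72.7% | 82.4% | −9.7 |
| 27, independent | 0.5 | 75.7% | 81.5% | −5.8 |
| 7, independent | 0.5 | 78.8% | 80.8% | −2.0 |
| 27, correlated 0.3 | 0.5 | 73.6% | 75.8% | −2.2 |
| 7, correlated 0.3 | 0 | 76.3% | 74.8% | +1.5 |

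A repeat put the top row at about 8 points below the fixed model and the bottom row at about 1 point above it. Size under the rule was 3.0% and 3.9% in the top two rows, and about 3.3 to 5.3% across settings in the repeat.

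**The case against.** A reader might infer that selecting covariates on the data breaks the 5% error rate. It does not when the rule is applied mechanically: size stayed at or below 5% within simulation error in every setting, because adjusting for unbalanced prognostic variables, or leaving out a stratifier, makes this test conservative. Inflation would require someone to choose which variables to test after seeing outcomes. The open wording permits that, but the document gives no sign of it and the simulations do not cover it.

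A reader might also infer that the stated 80% power fails. The article gives no SD, so that figure can be neither confirmed nor refuted. What the simulations compare is one model with another. Even that comparison rests on invented covariate strengths, and many of the measures (gait speed, grip strength, balance, frailty, activities of daily living) are likely to be correlated, which shrinks the gap.

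The 75% is the upper end of its range. The Charlson wording, that the index "will be applied to measure the burden of disease and thus enable confounder adjustment of the results", fits a rule under which the index is merely eligible. It is not a promise of fixed adjustment, so the two sections do not contradict each other.

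It is fair, too, that the likely strongest covariate, the baseline value, is fixed in advance; that the covariate sentence does not expressly exclude sex; and that a full analysis plan might name it. But the selection rule is a positive statement in the article, not a detail left out, and a plan that followed it would carry it forward. That part of the point stands.

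**Conclusion.** The point holds in a limited form. The rule selects on chance imbalance, leaves the sedentary-time model undefined until data are seen, and all but shuts out sex. The chance of at least one spurious covariate is about 30% with 7 independent candidates and up to about 75% with 27, at an assumed 5% selection level.

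The effect estimate stays unbiased and the size is nominal or conservative, about 3 to 5%. Against a fixed model with baseline value and sex, the loss is roughly 0 to 10 points of power in most assumed settings, largest when sex is strongly prognostic and candidates are many and independent. With few correlated candidates and a non-prognostic sex, the rule can be about 1 point better. Covariate strengths, correlations and candidate counts are all assumptions.

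Feasibility, the other primary outcome, is mainly descriptive and unaffected. For a feasibility trial with an unbiased estimate and no inflation, this should be fixed as a cheap improvement; it is not a defect that undermines the trial.

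**What to change.** Under Statistical analyses, state the model as an ANCOVA of sedentary time on arm, baseline sedentary time and sex, at 12 and at 24 weeks, and use the same form for the other continuous outcomes with their own baseline values. Delete the clause that admits covariates by baseline significance, and describe baseline characteristics without p-values. If adjustment for the Charlson index is wanted, name it in advance, either as a fixed covariate or as a sensitivity analysis.

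The cost is a change of wording and one degree of freedom for sex. No extra participants or data are needed. In some settings there will be no gain in power; what is gained in every case is a model fixed before the data are seen.
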